### Recruitment {15}

The primary method of recruitment will be via door knocking and lobby intercepts until we reach our targeted number of residents per group (4 smokers, 4 non-smokers in each building). We will make every attempt to retain participants and minimize attrition bias through a range of rapport building and retention techniques, incentives, and cultural adaptation of study materials. We have also powered the study based on 80% retention.

While the study presents minimal risks, participants may withdraw at any time upon request.

Alternatives available to participants outside the research context are simply not enrolling and attempting to serve the greater good by participating in other research or community service activities.

## Assignment of interventions: allocation

### Sequence Generation {16a}

A list of eligible buildings from each borough will be randomly ordered by computer-generated random numbers for each borough. Then, the first 24 buildings for each borough (n = 48, 24 per borough) will be randomly assigned to receive intervention A, B, or A + B.

Additionally, all buildings that are eligible for the study but have been identified by NYCHA as locations where they will conduct activities to promote the smoke-free policy will be randomly ordered by computer-generated numbers for each borough. Then, the first 8 buildings for each borough (n = 16, 8 per borough) will be assigned to serve as a control site.

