## Interventions

### Explanation For The Choice Of Comparators {6b}

Buildings and study participants assigned to the comparator arm [Arm 4] are recruited and followed over approximately a 12-month period to assess outcomes. No additional programs or services will be delivered to the buildings or residents assigned to this arm beyond standard programs that NYCHA may provide to support the smoke-free mandate. Field staff will document any policy-related signage, activities, or information to which these participants are exposed. We expect and have confirmed that Smoke-Free NYCHA’s liaison program will occur during our period of data collection during which they will conduct programming and activities that support compliance to the smoke-free policy. As such, the buildings enrolled in our ‘Standard NYCHA approach’ are buildings that the Smoke-Free NYCHA team has identified as locations for concentrated efforts of their own smoke-free programming over the course of our data collection period. We will therefore evaluate the impact of this parallel prevention program including a covariate for NYCHA study participation at baseline in the models specified below. We will further allow for an interaction between the NYCHA study participation indicator and the treatment group.

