## Statistical methods

### Statistical Methods For Primary And Secondary Outcomes {20a}

We will conduct intent-to-treat (ITT) and contamination-adjusted intent-to-treat (CA-ITT) analyses to estimate the effects of the smoking relocation/cessation and resident endorsement interventions compared to the standard program implemented by NYCHA (no treatment). CA-ITT analyses will account for unanticipated contamination between trial arms and be completed via two-stage instrumental variables regressions using the original random allocation codes per assigned unit. Preliminary data analysis will include examination of distribution and summary statistics of all variables by intervention groups at each time point. The continuous variables with skewed distribution will be properly transformed, if necessary, to reduce impact of extreme values or improve model fitting. We will use box-plots to examine how distribution of a quantitative variable varies by categories of a categorical variable, and use scatter plots and Spearman correlation coefficient to examine bivariate associations between quantitative variables. Chi-square and Kruskal-Wallis tests will be used to detect group differences in categorical and quantitative baseline variables, respectively. For successful randomization, we expect no difference in the distribution of all baseline variables among the four arms. The baseline variables that differ by intervention groups and are related to outcomes of interest will be controlled in the aim specific models.

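### Arm 4 is not randomised against arms 1–3: control buildings are sampled from a list NYCHA chose for its own smoke-free activities, and the planned NYCHA covariate and interaction do not repair this

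*Protocol article*

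**What the plan says.** Sequence Generation {16a} describes two separate draws. In the first, eligible buildings in each borough are randomly ordered and "the first 24 buildings for each borough (n = 48, 24 per borough) will be randomly assigned to receive intervention A, B, or A + B". In the second, eligible buildings that "have been identified by NYCHA as locations where they will conduct activities to promote the smoke-free policy" are randomly ordered and "the first 8 buildings for each borough (n = 16, 8 per borough) will be assigned to serve as a control site".

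Explanation For The Choice Of Comparators {6b} confirms that the control buildings are "buildings that the Smoke-Free NYCHA team has identified as locations for concentrated efforts of their own smoke-free programming". It proposes to deal with the parallel programme by "including a covariate for NYCHA study participation at baseline in the models specified below", and adds: "We will further allow for an interaction between the NYCHA study participation indicator and the treatment group".

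Other sections treat all four arms as randomised:

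- Trial design {8} calls the study a four-arm, factorial cluster RCT.
- Eligibility Criteria {10} says that buildings are randomised to an intervention or to act as control.
- Statistical Methods {20a} states "For successful randomization, we expect no difference in the distribution of all baseline variables among the four arms".
- The same section bases the contamination-adjusted analysis (CA-ITT) on "two-stage instrumental variables regressions using the original random allocation codes per assigned unit".
- The model under Primary outcome takes arm 4 as the reference group.

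**The concern.** Random ordering within the NYCHA list is random sampling of control buildings. It is not random assignment between control and intervention. A building enters arm 4 only if NYCHA picked it, and a building in the first draw has no chance of being a control. NYCHA's reasons for picking a building are not given, and they may be related to smoking levels, complaints, management or expected trends.

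Arm 4 enters all three comparisons with control, both with-versus-without factorial comparisons and the A×B test. If it is not exchangeable with the other arms, these analyses are observational, and the allocation code is not a valid randomised instrument for any of them. As the text stands, results would be reported as randomised evidence against the standard approach, which the allocation does not support.

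**Working it through.** **1. The figure that depends on a randomised arm 4.** Sample Size {14} gives detectable effects for an arm against control of 0.472, 0.499 and 0.524 SD at ICC 0.1, 0.15 and 0.2 (128 per arm, α = 0.05/3, two-sided, 80% power). With K clusters of m per arm, SE = √[2(1+(m−1)·ICC)/(K·m)], and power comes from a noncentral t with 2(K−1) df. With K = 32, m = 4 and ICC 0.1, SE = √(2×1.3/128) = 0.1425. The detectable effect is 0.472, and the other two values also match (0.499, 0.524). The section's own 16 buildings of 4 per aim give 0.685, 0.724 and 0.760. That discrepancy is a separate matter. What counts here is that the calculation assumes a cluster-randomised comparison with control.

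**2. Bias.** Let μ₁ to μ₄ be the mean changes the four arms would show in exchangeable buildings, with arm 3 the combined arm. Let observed change in arm 4 be μ₄ + d.

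- Arm h versus control: μₕ − (μ₄ + d), off by −d.
- Additive effect of A, equal arms: ½[(μ₁ + μ₃) − (μ₂ + μ₄ + d)], off by −d/2. The same holds for B.
- A×B interaction: μ₃ − μ₁ − μ₂ + (μ₄ + d), off by +d.
- A+B versus A, A+B versus B, A versus B: no d, so unaffected.

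The documents give no d. As an illustration only, assume that selection alone gives |d| = 0.1, 0.2 or 0.3 SD and that there is no true effect. At ICC 0.1, a nominal 0.0167 test of an arm against control then rejects with probability 0.029, 0.074 or 0.165 (16 clusters of 4), or 0.045, 0.153 or 0.368 (32 clusters of 4).

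**3. The NYCHA covariate in the four-arm model.** Suppose the indicator N is 1 in arm 4 buildings and 0 elsewhere, as the text implies. Then N = 1 − (arm 1 + arm 2 + arm 3). Over 64 buildings:

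| Terms | Columns | Rank |
|---|---|---|
| Intercept + 3 arm dummies | 4 | 4 |
| + N | 5 | 4 |
| + N × arm | 8 | 4 |

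N is aliased with the arm dummies, and every interaction column is zero.

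**4. The covariate in the additive A, B model.** Here N can be fitted (4 columns, rank 4). Since N = 1 − A − B + AB, it is the same term as the A×B interaction. With N in the model, arms 1–3 fix the other parameters: A is estimated as arm 3 minus arm 2, and B as arm 3 minus arm 1. Both are randomised contrasts. However, the effects of interest are the time-by-A and time-by-B terms. A covariate constant over time shifts only the level, so N must also be crossed with time before it changes those terms.

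**5. Other readings of the indicator.** Participation is not defined as building-level or person-level.

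| Reading | Rank with covariate | Rank with interaction |
|---|---|---|
| All arm 4 and a quarter of arm 1–3 buildings are NYCHA sites | 5 of 5 | 7 of 8 |
| Person-level, occurring only in arm 4 | 5 of 5 | 5 of 8 |
| Person-level, varying within all four arms | 5 of 5 | 8 of 8 |

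Under none of these is there a control building that NYCHA did not select, so selection and control status stay inseparable.

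**The case against.** A reader might infer that the planned NYCHA correction cannot be fitted at all. The documents do not support that. The coding in step 3 is implied but never stated. The first draw is not explicitly said to exclude NYCHA-identified buildings. Field staff are to document the policy-related activities to which control participants are exposed, so a person-level measure is possible. Even under the building-level coding, the main effect can be fitted in the additive model, where with time terms it would protect the A and B effects. What stands is narrower: the indicator is undefined, and under no reading does it separate building selection from control status.

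A reader might also count the whole effect of NYCHA's programme as bias. The declared comparator is NYCHA's standard approach, so that effect is at least partly what the trial sets out to compare against. The clear bias is selection. The no-treatment label in Statistical Methods {20a} can be read as no study treatment, and nothing in the documents ranks the intensity of programming across arms.

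There are real mitigations. The models estimate change since baseline, which removes fixed level differences between the two lists, and baseline variables that differ by arm and relate to outcome are to be controlled. Neither removes differential trends or unmeasured differences tied to NYCHA's choice of buildings.

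**Conclusion.** The point holds in this form. Only A, B and A+B are randomised, and arm 4 is a random sample from a NYCHA-selected list. Trial design {8}, Eligibility Criteria {10} and Statistical Methods {20a} contradict Sequence Generation {16a} on this. The bias sizes in step 2 follow from equal arms and a single shift in arm 4. The value and sign of d are unknown, and the rejection rates shown rest on assumed values. Contrasts with arm 4 estimate the effect against NYCHA's concentrated programming in buildings NYCHA chose, not against the absence of a programme. The remedy in {6b} does not restore a randomised comparison. Contrasts among the three intervention arms are sound.

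**What to change.** 1. In Trial design {8}, Eligibility Criteria {10}, Sequence Generation {16a} and Statistical Methods {20a}, state that only A, B and A+B are randomised and that arm 4 is a non-randomised concurrent comparison with NYCHA concentrated programming.
2. Report contrasts with arm 4, and factorial margins that use it, as non-randomised, adjusted for borough and baseline outcome. Identify A+B versus A and A+B versus B, both already in the hypothesis under Objectives {7}, as the randomised comparisons, and state their detectable effect. Arms are of equal size, so at α = 0.0167 the arm-versus-control figures in step 1 apply: 0.472–0.524 SD on 128 per arm, or 0.685–0.760 SD on 16 buildings of 4.
3. Remove the NYCHA-by-treatment-group interaction, and do not present the covariate as correcting the arm 4 contrast. If additive A and B effects are reported, include an arm 4 indicator and its time interactions so that A and B are estimated from the randomised arms. Alternatively, define a participation measure that varies within arms.
4. Restrict the CA-ITT instrumental-variable estimates to the randomised arms.

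No new data are needed, but the cost goes beyond wording. Claims against the standard approach become non-randomised evidence, and the control comparisons in Sample Size {14} lose their randomised interpretation.

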### Concealment Mechanism {16b}

The allocation of interventions is done on a building basis and will only be revealed to specific research team members and intervention implementors (PEs). This information will be passed to Health People via encrypted emails. All data collectors will not be informed of intervention assignment for the duration of the study.

### Implementation {16c}

[name] oversaw the allocation sequence and intervention assignment prior to the start of recruitment. Trained field-based research support staff are recruiting and enrolling participants in buildings that are enrolled in the study.

## Assignment of interventions: Blinding

### Who Will Be Blinded {17a}

Trial participants and outcome assessors are blinded after the assignment to interventions. All interventions are assigned at the building level. We have a separate field team research support staff who conduct recruitment and collect the assessments but are unaware of the assignments.

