#### Arm 1: Reduction (via relocation and reduction in personal smoking)/Cessation

The reduction/cessation arm (Arm 1) “meets smokers where they are” using a) a harm reduction approach that reinforces the use of designated smoking areas available and/or identifies ways residents can reduce their personal smoking more generally via motivational interviewing skills thereby encouraging compliance via relocation and personal smoking reduction; along with b) in-residence cessation support to reduce barriers to participation in cessation services. Enrolled participants who are smokers will be referred by the survey team to peer educators from Health People. The peer educator will coordinate smoking cessation support, including serving as a liaison between participant and research team, providing information regarding the smoke-free policy and opportunities for relocation, and connecting participant to tobacco replacement therapy and/or physician support if deemed appropriate.

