#### Arm 2: Resident Endorsement

The resident endorsement model (Arm 2) seeks to engage residents by using an empowerment/network-based approach to shift the culture of health in buildings that encourages residents to collectively tackle indoor smoking and secondhand smoke exposure via physical demarcations and/or social media. Buildings assigned to this arm will be targeted for a series of 2 in-residence programs that involve community forums and the creative arts to garner resident endorsements of smoke-free living environments. Premised on resident engagement, this arm seeks to impact social and physical dimensions of the residential environment to achieve compliance. The sessions will: 1) inform residents of risks associated with smoking and secondhand smoke; 2) identify reasons to have a smoke-free home, 3) ask residents to sign a pledge on paper and/or virtually; 4) display smoke-free signage on doors and/or social media pages with an original hashtag (#Smokefree[building address]); and 5) refer residents to the Smoke-free NYCHA website for information on the policy and existing cessation resources.

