### Procedure For Unblinding If Needed {17b}

Overall, the study has very minimal risks, and by its nature participants may know which intervention they/their building is receiving based on what services, if any, are provided and what materials are displayed, if any. Blinded data collectors may also guess the intervention based on what materials are displayed or not displayed. The intervention team, the peer educators will report any serious adverse events that occur during intervention implementation to the research team, but the identity of the participant and the intervention assigned to their building will not be revealed to data collectors.

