### Interviewer bias.

We will minimize interviewer biases, including social desirability bias, through highly structured questionnaires, training in standard probes, and other techniques. To specifically minimize social desirability bias, we will use introductory language to reinforce the neutrality of our interviewers and the questions they are administering as well as standardized questions to measure social desirability (72). We also do not inform the interviewers of the study hypotheses and employ blinding wherever possible.

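### The protocol states that participants are blinded, but the interventions are unconcealed and the protocol concedes that participants may know them, so the two self-reported primary outcomes are open-label

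*Protocol article*

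**What the plan says.** Who Will Be Blinded {17a} makes an unqualified statement: "Trial participants and outcome assessors are blinded after the assignment to interventions". The next section, Procedure For Unblinding If Needed {17b}, says that "by its nature participants may know which intervention they/their building is receiving based on what services, if any, are provided and what materials are displayed", and adds: "Blinded data collectors may also guess the intervention based on what materials are displayed or not displayed".

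Concealment Mechanism {16b} sets out the procedure for assessors: "All data collectors will not be informed of intervention assignment for the duration of the study". {17a} adds that recruitment and assessments are done by a separate field team.

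The intervention sections describe what participants see. In Arm 1, smokers work with a peer educator on relocating, reducing or stopping smoking, and those interested in quitting receive nicotine patches (Provisions For Post-trial Care {30}). Arm 2 holds in-building sessions that, among other things, "ask residents to sign a pledge on paper and/or virtually" and put smoke-free signs on doors or social media. Arm 3 receives both. The comparator arm receives nothing from the study beyond the housing authority's own programme (Explanation For The Choice Of Comparators {6b}).

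Outcomes {12} lists three primary outcomes. Cigarettes per day and secondhand-smoke exposure are self-reported. The third, salivary cotinine, is measured in 25% of the sample.

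**The concern.** Participant blinding is presented as a feature of the design, and the design does not have it. This matters because for cigarettes per day and secondhand-smoke hours the participant is the source of the measurement. An interviewer who does not know the arm still records what an unblinded respondent chooses to say.

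Misreporting may then depend on arm. Someone who has been counselled to cut down, or has signed a pledge, has a reason to report less smoking. Someone taught about secondhand smoke may notice and report more exposure. The direction of bias is therefore fairly predictable for cigarettes per day and uncertain for secondhand smoke. A difference between arms on either outcome could reflect reporting, behaviour or both, and the statement in {17a} suggests that the first has been dealt with.

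**Working it through.** **1. The two statements side by side.** {17a} says participants are blinded after assignment. {17b} says they may know their intervention from the services and materials. Both are current text under the same blinding heading. The arm descriptions settle which is accurate: counselling, patches, pledges and signs cannot be hidden from those who receive them, and no sham is described for controls.

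**2. Who is exposed to an unconcealed component** (Trial design {8}: 16 buildings per arm, 4 smokers and 4 non-smokers per building):

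- Arm 1 smokers: 16 × 4 = 64
- Arm 2, everyone: 16 × 8 = 128
- Arm 3, everyone: 16 × 8 = 128
- Total: 320 of 3 × 128 = 384 intervention-arm participants (83%)
- No direct component: 16 × 4 = 64 Arm 1 non-smokers, and the 128 controls

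These are people offered or targeted; actual uptake is not known.

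**3. Reach of the objective measure.** The protocol's figure reproduces: 64 × 8 = 512 and 0.25 × 512 = 128. That is 128 / 4 = 32 per arm, or about 16 per arm in each smoking stratum if split evenly (assumption). It is collected at baseline and 12 months, not at 3 months.

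**4. Illustration of size for cigarettes per day.** The protocol gives no mean or SD for this outcome and no misreporting rate, so these are assumptions: mean 10 and SD 7 cigarettes/day, and 5–10% extra under-reporting, equal in all three intervention arms. The ICC of 0.1 is the lowest of the three values in Sample Size {14}. Full retention is assumed, and the SD is taken as that of the analysed outcome.

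- Bias per intervention arm: d = 0.5/7 to 1.0/7 = 0.071 to 0.143 SD
- Factorial contrast for A: Arms 1 and 3 against Arms 2 and 4. Arm 2 is also an intervention arm, so the contrast bias is (d + d)/2 − (d + 0)/2 = d/2 = 0.036 to 0.071 SD. The B contrast gives the same.
- Smokers per side: 32 buildings × 4 = 128
- SE = √[2(1 + 3 × 0.1)/128] = 0.143 SD
- Bias/SE = 0.25 to 0.50
- Chance of a significant result with no true effect: Φ(bias/SE − 1.96) + Φ(−bias/SE − 1.96) = 5.7% to 7.9%, against a nominal 5%

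For one arm against control the full d applies, with 64 smokers per arm and the protocol's alpha of 0.0167. SE = √[2 × 1.3/64] = 0.202 SD, bias/SE = 0.35 to 0.71, and the same formula with critical value 2.394 gives 2.4% to 4.7%, against a nominal 1.67%.

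**The case against.** Several points on the other side are sound.

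- **The problem is disclosed.** {17b} follows directly and admits both that participants may know and that collectors may guess. This is a contradiction, not concealment. A reader might infer that anyone reading the protocol would be misled; a careful reader would not be. The false sentence still stands, and it is the one likely to be carried into reports.
- **Assessor blinding is not empty.** A reader might infer that all blinding fails. The documents do not support that: separate staff are not told the assignment, and interviewers are not told the hypotheses (Interviewer bias). The procedure is imperfect because materials are on display. The Arm 1 text, "Enrolled participants who are smokers will be referred by the survey team to peer educators from Health People", also leaves it unclear whether those making referrals are the same staff who must stay unaware.
- **Not every reporter is affected.** Arm 1 non-smokers receive no direct component, so the Arm 1 versus control comparison of secondhand-smoke hours in non-smokers is much less exposed.
- **Safeguards exist.** The protocol plans "standardized questions to measure social desirability", collects cotinine to check self-report, and plans regression calibration for imperfect reliability (Secondary outcome and Sensitivity analyses). The text does not say that the calibration lets error differ by arm, which is the error that unblinding creates. How the social-desirability items enter a model may properly be left to an analysis plan that is not shown, so that silence is not a fault.
- **The size is easily overstated.** A reader might put the whole of d into the factorial contrast. That requires the bias to attach only to the component contrasted, or to add up across components in Arm 3; the documents say neither. Nor can 256 per side be used for cigarettes per day, since only the 4 smokers per building contribute.

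The interventions cannot realistically be masked, so the choice of an unblinded design is not itself a fault.

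**Conclusion.** The point holds as a false design statement with a real but moderate consequence. Participants are not blinded, {17a} says that they are, and keeping collectors unaware does not protect the two self-reported primary outcomes. The contradiction needs no calculation and rests only on the protocol's own text.

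The numerical consequence depends on assumptions. With equal under-reporting of 5–10% in all intervention arms, the false-positive rate of a factorial contrast in smokers rises from 5% to about 6–8%. Larger or component-specific bias would raise it further, but nothing in the protocol fixes those values.

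A reader might go on to infer that a self-reported benefit should count only if cotinine moves the same way. The documents do not support so strict a rule: with about 16 samples per arm per stratum, the sign of the cotinine difference is too noisy to act as a gate.

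**What to change.** 1. Replace the sentence in {17a} with a statement that participants are not blinded, and that data collectors are not told the assignment but may infer it from displayed materials. Reconcile this with {17b}, and clarify in the Arm 1 text who makes the referral to peer educators.
2. Label cigarettes per day and secondhand-smoke hours as open-label self-report, open to reporting bias that may differ by arm, and note that Arm 1 non-smokers are less affected.
3. As a sensitivity analysis, use the social-desirability items and the cotinine subsample to examine whether self-report error differs by arm. Present it as descriptive, given the subsample size. Adjusting for a baseline social-desirability score alone would not be enough, because it does not remove bias that the intervention itself induces.

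The cost is protocol wording and one analysis of data already planned. The downside is a less favourable description of the trial's blinding and a more cautious claim for the self-reported outcomes.
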